#### Socioeconomic and demographic information

2.4.1

The following demographic and personal information based on will be collected [43]: gender (male/female), age (continuous variable in complete years), marital status (married, cohabiting, single, divorced/separated, widowed), education level (never attended school, reads and writes their name, primary school: 1st to 4th grade, lower secondary school: 5th to 8th grade, high school: 1st to 3rd year, higher education: completed, incomplete, 3rd to 4th year), race/ethnicity (white, yellow (oriental), mixed race, indigenous origin, black, unknown), number of living children (variable in Arabic numerals), housing characteristics (living with others, living alone, no response, unknown), religion (Catholic, Protestant, Jewish, Spiritus/Kardecist, Umbanda, Other), average per capita family income (quantified in Brazilian Reais R$, *2022: minimum wage R$ 1302.00), and occupation (yes or no).

#### Brain health

2.4.2

For the assessment of cognitive status, the Brazilian version Mini-Mental State Examination (MMSE) will be employed. The MMSE evaluates five cognitive domains on a 30-points (pts) scale, including orientation, immediate recall, attention and calculation, delayed recall, and language [44]. Participants will be classified into cognitive profiles using the criteria described by Mungas: a) Severe Cognitive Impairment [01 to 09 pt]; b) Moderate Cognitive Impairment [10 to 18 pt]; c) Mild Cognitive Impairment [19 to 24 pt]; d) Normal Cognitive Profile [ 25 to 30 pt]. The World Health Organization's Self Report Questionnaire (SRQ-20) will be utilized for screening common mental disorders (CMDs) [45]. Validation studies in Brazil have demonstrated the SRQ-20's effectiveness in identifying potential CMDs, and the cutoff point of seven and five positive responses will be adopted to classify individuals, as having or not having CMDs [46].

#### Physical fitness

2.4.3

The Short Physical Performance Battery (SPPB) will be used to evaluate physical function through three tests [47]: 1) Balance Test: Participants will be assessed in three positions - feet side by side, semi-tandem, and tandem - with the evaluator measuring the time they can maintain each position. Scores range from 0 to 2.2) 4-Meter Gait Speed Test: Participants will walk the distance three times, and the fastest time will be recorded. Scores range from 0 to 4.3) Sit-to-Stand Test: Participants will perform sit-to-stand movements for 30 s, with scores ranging from 0 to 4 based on the number of repetitions completed. The total SPPB score will be the sum of the scores from all three tests, ranging from 0 to 12. Participants will be classified as having poor (0–3), low (4–6), moderate (7–9), or good (10–12) physical capacity based on their total score [48].

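### SPPB (section 2.4.3): the stated balance range of 0–2 does not reconcile with the stated 0–12 total and its bands; the sub-scores as written sum to at most 10

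*Protocol article*

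**What the plan says.** All the figures stand in one paragraph of the protocol article, section 2.4.3 (Physical fitness). The list numbers of the second and third tests are run together with the preceding score ranges.

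- Balance, 0 to 2: "Scores range from 0 to 2.2) 4-Meter Gait Speed Test". The second 2 is the list number of the gait test.
- Gait speed, 0 to 4: "Scores range from 0 to 4.3) Sit-to-Stand Test". The 3 is the list number of the sit-to-stand test.
- Sit-to-stand, 0 to 4: "with scores ranging from 0 to 4 based on the number of repetitions completed".
- Total: "The total SPPB score will be the sum of the scores from all three tests, ranging from 0 to 12".
- Classification: "poor (0–3), low (4–6), moderate (7–9), or good (10–12) physical capacity based on their total score".

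The balance test has three parts: "Participants will be assessed in three positions - feet side by side, semi-tandem, and tandem". The evaluator times each position, but the article gives no maximum for any single position. No other section gives a different balance range, or a weighting that would turn these three sub-scores into a 12-point total.

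**The concern.** A total defined as a plain sum must have a maximum equal to the sum of its parts' maxima. Here it does not, so a reader cannot tell which figure an assessor would follow.

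The SPPB is the instrument described under Physical fitness. Section 2.1 plans a pre- and post-intervention comparison of physical variables, and section 2.9 converts changes in all variables to standardized effect sizes. The scoring rule therefore affects the numerical outcome as well as the descriptive label. The exercise arm trains balance in its first block (section 2.6.1), and a 0–2 balance score would leave less room for a change in balance to show.

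Scored data may already exist. Section 2.8 reports in the past tense that functional tests were administered in the pilot, and section 2.4 describes the baseline instrument in the past tense. Section 2.6.5 also foresees use of the programme elsewhere in Brazil, in Portugal and in Mozambique, where teams may follow the published text.

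**Working it through.** **Inputs** (all from section 2.4.3): balance maximum 2, gait maximum 4, sit-to-stand maximum 4, stated total maximum 12; bands poor 0–3, low 4–6, moderate 7–9, good 10–12.

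**1. Try to reproduce the stated maximum of 12.**

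| Reading of the balance range | Sum | Result |
|---|---|---|
| 0–2 for the whole test | 2 + 4 + 4 | 10 |
| 0–2 for each of three positions | (3 × 2) + 4 + 4 | 14 |
| Run-together figures taken as decimals | 2.2 + 4.3 + 4 | 10.5 |

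None of these gives 12. With the other two ranges as stated, the balance maximum that gives 12 is 12 − 4 − 4 = 4.

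**2. Which figure is out of line.** The total (0–12) and the bands (ending at 12) agree with each other. The balance range agrees with neither.

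**3. Consequence if balance is scored 0–2 and the bands are applied as printed.**

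- Totals of 11 and 12 cannot be reached. The top band reduces to the single value 10, which is a perfect score on every test.
- In whole-number sub-scores there are 3 × 5 × 5 = 75 combinations, of which 1 reaches 10. With balance 0–4 there are 5 × 5 × 5 = 125, of which 10 reach 10 or more (1 with total 12, 3 with 11, 6 with 10).
- Balance supplies 2/10 = 20 % of the maximum, against 4/12 = 33 % with a balance maximum of 4.

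**4. A participant with full balance.** Scored 2 rather than 4, this person's total falls by 2:

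| Total with balance = 4 | Band | Total with balance = 2 | Band |
|---|---|---|---|
| 4, 5 | low | 2, 3 | poor |
| 6 | low | 4 | low |
| 7, 8 | moderate | 5, 6 | low |
| 9 | moderate | 7 | moderate |
| 10, 11 | good | 8, 9 | moderate |
| 12 | good | 10 | good |

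There are 5 × 5 = 25 pairs of gait and sit-to-stand scores. The pairs giving totals of 4, 5, 7, 8, 10 and 11 number 1 + 2 + 4 + 5 + 3 + 2 = 17. The band therefore drops by one in 17 of 25 pairs. These are counts of score combinations, not expected proportions of participants; the article gives no SPPB distribution from which to estimate those.

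**The case against.** **The 0–2 range may describe scores across positions.** The range follows a sentence about timing each position. If the three positions had unequal maxima such as 1 + 1 + 2 = 4, the total would be 4 + 4 + 4 = 12, as stated. This is possible, but the article gives no per-position maxima, and it words the range for the single gait test in the same way. Even on this reading, the balance sentence fails to tell an assessor how to reach 12 and needs rewording.

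**A misprint harms nobody.** This stands. A reader might infer that the total and bands are wrong and that participants are being misclassified. The document does not support that: the total and bands are mutually consistent, and misclassification arises only if balance is actually scored 0–2.

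**The rank of the outcome.** A reader might take the SPPB as a main outcome. The article does not give it that rank. The Introduction names raising physical activity levels as the purpose and the RE-AIM assessment as the secondary objective, with functional fitness in a list of further indicators.

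**No downstream use of the bands.** This also stands. They are not an eligibility criterion (section 2.2), they play no part in the sample size given there, and section 2.9 does not name them as an analysis variable. If both arms and both visits are scored by the same rule, the inconsistency does not by itself show bias in the between-arm comparison. What would be lost is balance weight and resolution, and the meaning of the labels.

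**Comparability with the cited battery.** A reader might add that scores would not be comparable with that source. It is not at hand, so the point is not made here; the internal sum is enough.

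**Conclusion.** The inconsistency is real and is settled by arithmetic within one paragraph: the parts reach 10, the stated total is 12, and the gap is the 2 points by which the balance maximum falls short of 4. The effect on participants is conditional. If balance is scored 0–2 and the printed bands are used, the top band narrows from three values to one, and a participant with full balance drops one band in 17 of 25 score pairs. If assessors score balance 0–4, there is no effect beyond the wrong text.

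The band shifts assume whole-number sub-scores, the bands as printed, and full balance earning the maximum on either scale. Which scoring is in use cannot be determined from the article. This is a should-fix correction to an outcome definition. It does not touch the sample size or the choice of tests.

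**What to change.** Reconcile section 2.4.3 in one of two ways:

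- state the balance range as 0–4, with the points for each position, so that the three parts sum to 12 and the printed bands apply; or
- if 0–2 is intended, restate the total as 0–10 and do not apply the 0–12 bands.

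Confirm with the assessors which scoring was used in the pilot and at baseline, and use one rule for both arms and both visits. If any data were scored 0–2 and the 0–4 scale is adopted, re-score them where the balance hold times were kept. The article says these times are measured but not that they are stored, and it gives no time cut-offs, so both need checking first.

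The cost is a correction of a line or two and one query to the assessment team, plus re-scoring only if that query shows it is needed.

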#### Risk of falls

2.4.4

The risk of falls will be evaluated using three tests: i) a one question where participants will report if they had recent falls [49]; ii) the Timed Up and Go (TUG) test, measuring the time taken to rise from a chair, walk [50]; iii) and sit back down; and the 6-Meter Gait Speed Test, assessing walking speed. These tests will help identify individuals with a moderate risk of falls based on specific time cutoffs. Additionally, participants will have the option to choose between the 6-min walk test or the 2-min stationary march to evaluate aerobic endurance. The assessments require simple instruments such as a chair, measuring tape, and stopwatch, making them feasible for the study's participants [51].

#### Daily life functional tasks

2.4.5

Functional capacity related to activities of daily living will be assessed using the Functional Activities Questionnaire [52]. This instrument evaluates instrumental activities of daily living such as managing personal finances, cooking, and understanding one's environment, among others. The questionnaire consists of 10 questions, and each question allows the interviewee to score from 0 to 3 points. The adopted cutoff points are: 0 to 4 points = independent and ≥5 points = dependent. The questionnaire will be answered by the elderly participants, provided they do not exhibit cognitive impairments [53].

#### Daily life functional tasks

2.4.6

Anthropometric measures will follow standard procedures in accordance with guidelines cited in previous studies [54]. The measurements will be conducted in a separate room to provide privacy to the participants. Body mass weight will be determined using a portable digital scale (Omron®) with a precision of 0.1 kg. Waist, hip, and calf circumference will be measured using a retractable tape measure (Sanny®) with a precision of 0.1 cm. Stature will be determined using a portable stadiometer (Sanny®) with a precision of 0.1 cm.

#### General health status

2.4.7

Information on self-reported diseases related to the circulatory, respiratory, and musculoskeletal systems, medication use, and lifestyle habits such as alcohol consumption, tobacco use, and dietary patterns will be collected. In addition, will be measured using the digital sphygmomanometer by Omron® (HEM 705CPINT) before and after the intervention [55]. Participants will be asked to rest for 5 min in a seated position, and all measurements will be taken on the right arm of the participants [56,57].

#### Levels of physical activity

2.4.8

To assess mean daily physical activity (MDPA) in the elderly population, we will use the adapted and validated International Physical Activity Questionnaire (IPAQ) [58]. The questionnaire includes 15 questions in five domains, covering various dimensions of physical tasks, including work-related, transportation, household chores, recreational activities, and sitting time [59]. The total weekly physical activity will be calculated according to WHO guidelines, with individuals classified as active if they engage in 150–300 min of moderate and/or vigorous activity per week [60]. This comprehensive assessment aims to provide valuable insights into the levels of physical activity among the elderly participants and contribute to understanding their overall activity patterns and sedentary behavior for health promotion purposes [61].

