## Abstract

The EISI study protocol aims to address the low participation rate in physical exercise programs among older individuals, emphasizing its significance as a non-pharmacological therapeutic approach for overall health and increased physical activity. The objectives include implementing physical activity (PA) and educational health programs in Jequié, Bahia, Brazil, targeting the Family Health Strategy population to enhance local physical activity levels among older individuals. The study also seeks to evaluate the program's feasibility, safety, and sustainability for large-scale implementation, along with assessing its impact on immune and inflammatory response biomarkers to the SARS-CoV virus, as well as physical-functional and brain health. Participants, aged 60 or above, will be divided into two groups: multicomponent exercise (MCE) and behavioral change interventions (BCI). The study employs a mixed-method approach, utilizing a non-randomized controlled short-term pathway model for a 4–8 weeks of pilot study and 16-week intervention impact assessment. Data collection encompasses various aspects such as sociodemographic information, mental health, physical fitness, fall risk, functional capacity, anthropometric measurements, hemodynamic assessment, habitual physical activity, and health-related quality of life. Blood and saliva samples are collected for cytokine and antibody biomarker analysis related to SARS-CoV immunity. Pre- and post-intervention evaluations for both groups will be conducted, with the hypothesis that MCE will yield more favorable responses compared to BCI. The study's holistic approach, including the assessment of feasibility, safety, and sustainability, aims to contribute to achieving Sustainable Development Goals (SDG) 3 and SDG 9 b y promoting accessible and sustainable healthcare initiatives for older individuals. This research aligns with global efforts to enhance health and well-being, emphasizing the importance of regular exercise in the aging population.

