The Intervention Study Protocol in Older Health (EISI-SP) aims to implement a physical exercise program for users of the Family Health Strategy in the municipality of Jequié, Bahia, Brazil, with the purpose of increasing LPA in the local population. As a secondary objective, this program will be assessed using the RE-AIM model to determine its feasibility and sustainability for large-scale implementation. Furthermore, at the end of the program, which will span 8 weeks of intervention with a multicomponent exercise and behavioral change approaches, the impact on several metabolic, immune, functional physical fitness, psychological well-being, and mental health indicators will be evaluated.

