#### – MEP intervention

2.6.1

The MEP programs will be conducted by exercise specialists. The guidelines of the ACSM for exercise prescription in older adults will be followed [71]. Additionally, the recommendations of the Vivi Frail Program will also be adhered to Ref. [72]. There will be a total of 36 sessions, with a frequency of 2 times per week, spanning a period of 4 months. Each session will last for 50 min, divided into three blocks. The first block, lasting 10 min, will consist of aerobic and balance exercises. The second block will focus on 30 min of neuromuscular exercises, and finally, the last 10 min will be dedicated to cool-down exercises with stretching routines. Examples of the exercises to be performed are described in Fig. 2.

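### The definition of active is a closed band of 150–300 minutes per week, so read as written it excludes anyone above 300 minutes and any reported proportion active can fall as activity rises

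*Protocol article*

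**What the plan says.** Section 2.4.8 (Levels of physical activity) uses an adapted IPAQ, the only instrument the article lists for level of physical activity. It is described as "covering various dimensions of physical tasks, including work-related, transportation, household chores, recreational activities, and sitting time". Two quantities come from it. One is a total: "The total weekly physical activity will be calculated according to WHO guidelines". The other is a class, "with individuals classified as active if they engage in 150–300 min of moderate and/or vigorous activity per week". The article gives no class for values above 300 minutes and does not present 150 as a minimum.

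The Introduction describes the exercise programme as one "with the purpose of increasing LPA in the local population", and the Abstract says the programmes are meant "to enhance local physical activity levels among older individuals".

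Section 2.9 (Statistical data analysis) plans a t-test or Wilcoxon test and standardised effect sizes. It does not mention the active class.

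**The concern.** A classification meant to show whether people become more active should never score a person lower for doing more. A rule with both a floor and a ceiling breaks that principle: moving up through 150 minutes gains active status, and moving up through 300 minutes loses it. A proportion active built on the rule is therefore non-monotone in activity. It could rise, stay flat or fall while every participant does more.

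Values above 300 minutes are not far-fetched. The questionnaire covers work, transport, household and leisure activity. The eligibility criteria (section 2.2) screen out people already in structured exercise programmes, but not people with a lot of other activity.

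At stake is any table or statement giving the share of participants who are active before and after the programme. The Introduction cites such a share for older Brazilians as part of the motivation, so the study could well report one too.

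**Working it through.** The plan states no sample size, power or error rate that depends on this rule, so there is no figure to reproduce. The check applies the rule as printed and compares it with a floor-only rule.

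**Rules**
- Band, as printed in section 2.4.8: active if 150 ≤ minutes ≤ 300.
- Floor only: active if minutes ≥ 150.

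**Step 1. A case that needs no assumption about classes.** A participant moves from 280 to 320 minutes. Band: active, then not active. Floor only: active both times.

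**Step 2. Minutes the classes could add.** Section 2.6.1 gives the inputs: "Each session will last for 50 min, divided into three blocks", "with a frequency of 2 times per week". The last block is 10 minutes of cool-down stretching.
- All class time: 2 × 50 = 100 min/week.
- Without the cool-down: 2 × (50 − 10) = 2 × 40 = 80 min/week.

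**Step 3. Baselines carried over the ceiling, if class time counts and nothing else changes.** A baseline that is active (at most 300) becomes not active when baseline + added minutes > 300.

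| Added min/week | Baselines that lose active status | Follow-up values | Baselines that gain active status |
|---|---|---|---|
| 100 | 201–300 | 301–400 | 50–149 |
| 80 | 221–300 | 301–380 | 70–149 |

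Under the floor-only rule nobody in the second column loses active status, and the last column is unchanged.

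**Step 4. Does class time enter the follow-up value?** Section 2.4 (Assessments) puts the second assessment one week after the programme ends, and the article does not state the questionnaire's recall period. If that period were the preceding week (an assumption), class minutes might not be counted at all. Step 3 is therefore conditional; Step 1 is not.

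**Step 5. Weight of one person.** Section 2.2 plans a minimum of 24 per group, which allows for adherence, from a base of 20. One reclassified person moves a group's proportion by 1/24 = 4.2 points, or 1/20 = 5 points.

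**Step 6. Illustration at group level.** The article gives no distribution of weekly minutes. Assume it is lognormal and that everyone adds 100 minutes. With a log-scale SD of 0.6, the share active changes as follows:

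| Baseline median (min/week) | Band, before to after | Floor only, before to after |
|---|---|---|
| 150 | 38% to 65% | 50% to 97% |
| 200 | 43% to 49% | 68% to 99% |
| 250 | 42% to 35% | 80% to nearly 100% |
| 300 | 38% to 25% | 88% to nearly 100% |

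Over 18 scenarios (medians 80, 120, 150, 200, 250 and 300; log-scale SD 0.6, 0.8 and 1.0), the change under the band ran from +59 to −13 points and was negative in three, all with a median of 250 or 300. Under the floor it ran from +12 to +64 points and was never negative. These figures show the direction of the distortion; they do not predict results in this trial.

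**The case against.** The strongest reply is that the range is shorthand for a recommended weekly amount. The text ties the calculation to WHO guidelines, does not say that only people inside the range are active, and never labels those above it inactive. This is probably what the authors meant. It does not remove the point, because the sentence is written as a classification rule and anyone coding it literally would build in the ceiling. Other scales in the same article are complete: the daily activities questionnaire (section 2.4.5) has an open-ended upper class, and the physical performance battery (section 2.4.3) assigns every possible total to a class.

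A reader might go further and infer that the ceiling spoils the outcome that carries the study's main aim, or that the most active participants will be counted as failures. The documents do not support either reading. No formal primary outcome is named, and no passage makes the proportion active an endpoint. The aim concerns the level of activity, and the planned tests suit quantitative scores. A reader might also object that dichotomising throws information away in a small study. That does not hold either: section 2.4.8 derives total weekly activity alongside the class, and nothing says the class replaces it.

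It is also fair to say that the frequency of harm is unknown. In the illustration the band reverses the direction only when the assumed baseline median is high.

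**Conclusion.** The concern holds in a limited form. As printed, the rule for active has an upper limit of 300 minutes and leaves higher values unclassified or, read literally, not active. A rise such as 280 to 320 minutes is then scored as a loss, against the programme's stated purpose. The damage is confined to the active/not active classification and any proportion derived from it; a comparison of total weekly minutes is untouched.

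If class time counts, the baselines at risk are about 221–300 minutes (80 minutes added) or 201–300 minutes (100 minutes added). That rests on class time being captured at a follow-up held after classes have stopped, which the article leaves unclear. How many participants would be affected cannot be determined, because no baseline distribution is given. The point is a wording error in a stated rule, worth correcting before anyone codes the variable.

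**What to change.** In section 2.4.8, define active as at least 150 minutes of moderate and/or vigorous activity per week, with no upper limit. If 300 minutes is wanted as a further cut, make more than 300 minutes a separate, higher class that still counts as active.

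The cost is one line of outcome definition. The questionnaire, the visits, the derived total and the planned tests stay as they are, and no new data are needed.
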